### *Clinically Emergent Patient Condition*

Should a matter be emergent, then 9-1-1 will be called and the patient will be brought to the hospital immediately. An example of an emergent patient condition is severe new-onset shortness of breath.

### *Clinically Urgent Patient Condition*

Should a matter be urgent, the patient and/or nurse/paramedic and/or physician may choose to communicate via phone or video (either of the 3 persons can initiate either medium). If this is unsuccessful, the nurse/paramedic will attempt to visit the patient in their home. If there is no way to rectify the situation, then the patient will be transported to the hospital. An example of an urgent situation is new-onset non-severe pain.

### *Unsafe Home Situation*

Should an unsafe home situation be discovered during a home hospital admission, the home hospital team will assess if said situation poses a harm or threat to either the participant or the home hospital personnel. If it does, and after an attempt to rectify said situation, the situation persists, then the home hospital team will end the study and transport the patient to the hospital. An example of an unsafe home situations includes lack of basic sanitation.

### *Intoxication*

Should intoxication occur in the home of a participant, the home hospital team will assess if said intoxication poses a harm or threat to either the participant or the home hospital personnel. If it does, and after an attempt to rectify said intoxication, the situation persists, then the home hospital team will end the study and transfer the patient to the hospital.

### *Neglect or child abuse*

Should neglect or child abuse be observed, the home hospital team will act as mandatory reporters. The home hospital team, in coordination with the hotline team, will assess if said neglect or child abuse poses an immediate harm or threat to either the participant, children in the home, or the home hospital personnel. If it does, then the home hospital team will end the study and transport the patient to the hospital.

### *Refusal of care*

Should an enrolled subject refuse standard care at their home despite a clear discussion with the home hospital team, then the subject will be transferred back to the treating hospital and formally withdrawn from the study.

## **6.0 BIOSTATISTICAL ANALYSIS**

### **6.1 Quantitative**

We will present descriptive data with counts and percentages, means and 95% CIs, or medians and interquartile ranges, as appropriate.

The primary outcome (hospitalization cost) will be analyzed between arms, adjusted for site as a fixed effect, which accounts for difference across the three sites. . However, we will present cost data as the percentage of change in mean costs from control (rather than absolute difference) because of the sensitive nature of these data. The primary outcome will be assessed using a generalized linear model assuming a gamma distribution with a log link, given the skewed nature of cost, with treatment arm (control arm as the reference group) and site as fixed effects. The exponential of the treatment effect in this gamma regression model exactly equals the effect of interest (the percentage change from control). Patient characteristics should balance out across the two arms due to randomization, but if not, in the gamma regression, we will adjust for any of the follow patient characteristics that differ across arms: sex, age (continuous), education, and comorbid condition count (continuous). We *a priori* plan to also adjust for COVID case burden at each hospital only if COVID impacted home hospital operations. If the degree of rurality was different between patients at different sites, we *a priori* plan to adjust for degree of rurality.

We will use this same multivariable regression approach for secondary outcomes, using logistic regression for binary outcomes (e.g., readmissions) and negative binomial regression for count outcomes such as days at home, and non-transformed linear regression for normally distributed continuous outcomes (e.g., days at home), as appropriate. Given the multiple comparisons, we will use the Benjamini-Hochberg method for multiple comparisons for the secondary outcomes, with 0.2 as a prespecified false discovery rate.

We *a priori* plan to perform a subgroup analysis that does not involve any extreme outlier participants (upper quartile plus 3 times the interquartile range) in either study arm, should this occur. We also *a priori* plan subgroup analyses by diagnosis, by age group, and by daily activity level. We may choose to employ non-parametric tests of significance should our data be nonparametric. We *a priori* plan to perform a subgroup analysis between continuous monitoring and intermittent monitoring sites. We *a priori* plan to perform a subgroup analysis by admission source (“from ED” vs “from ward” vs “from home”). We also plan to perform a secondary a priori subgroup analysis of US vs Canada.

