### 3.3 Source of subjects and recruitment methods

All subjects will be associated with rural hospital sites. This study will have three study sites, two U.S. based sites, and one site based in Canada.

Mass General Brigham will serve as the single-site IRB for the U.S. sites. The two U.S. study sites will be:

- Blessing Health System, IL
- Appalachian Regional Healthcare System, KY

The third study site has received local IRB approval for this study (approval certificate is attached in Insight)

- Alberta Health Services, AB, Canada (Wetaskiwin hospital)

A patient may be considered for RHH care if they are acutely ill at home, present acutely ill to a clinic or emergency department, or if they are admitted and require additional days of acute care (“early transfer”):

- If at home: this patient phenotype is well-known to her/his physician and has an acute illness of highly likely etiology (e.g., heart failure or chronic obstructive pulmonary disease exacerbation). The patient’s care team (perhaps primary care or a specialist) will receive a call from the patient describing acute symptoms. The care team will call the RHH clinical coordinator to describe the case. If appropriate, her/his physician will ask the patient if the research assistant/coordinator can approach the patient regarding the rural home hospital study. If the patient agrees, the research assistant/coordinator will call the patient to determine eligibility and introduce the rural home hospital to the patient, and explain randomization. If the patient is eligible and interested in participating, the RHH MD or RHH Advanced Practice Provider (APP) will make the decision to admit and will consent the patient. If randomized home, the RHH nurse/paramedic will meet the patient in their home.

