| Home health aide prior to admission          | RA via patient          | Admission       |
| Elective and urgent admissions in the        | RA via EHR and          | Admission       |

|                                                               |                                                                                 |           |
|---------------------------------------------------------------|---------------------------------------------------------------------------------|-----------|
| previous year, #                                              | patient                                                                         |           |
| ED visits in the previous 6 months, #                         | RA via EHR and patient                                                          | Admission |
| Interqual disease-specific leveling                           | MD                                                                              | Admission |
| PRISMA-7                                                      | RA via patient                                                                  | Admission |
| Eight-item Interview to Differentiate Aging and Dementia      | RA via patient or proxy                                                         | Admission |
| Would you be surprised if this patient died in the next year? | RA via MD                                                                       | Admission |
| BRIEF health literacy screening tool                          | RA via patient                                                                  | Admission |
| Readmission risk score on discharge (HOSPITAL)                | RA via EHR                                                                      | Discharge |
| Admitting diagnosis                                           | RA via EHR/MD                                                                   | Admission |
| Admission source                                              | RA via EHR/MD                                                                   | Admission |
| COVID case count on day of admission                          | RA via EHR                                                                      | Admission |
| Degree of rurality                                            | 2010 U.S. Census data, U.S RUCA codes/data files, population density, zip codes | Admission |

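### Admission source is known before randomisation and already collected, but it is left out of the primary cost model and its list of possible adjusters, which may give away precision

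*Protocol*

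**What the plan says.** - **Primary model (Protocol 6.1).** Hospitalization cost is analysed by gamma regression with a log link, "with treatment arm (control arm as the reference group) and site as fixed effects".
- **Permitted adjusters (6.1).** Sex, age, education and comorbidity count enter only if they differ between arms. For COVID the protocol says "plan to also adjust for COVID case burden at each hospital only if COVID impacted home hospital operations". Rurality enters on the condition "If the degree of rurality was different between patients at different sites". Admission source is in none of these.
- **Entry routes (3.3 and 4.1).** Patients may enter from home, a clinic or the emergency department. They may also enter from the ward, "if they are admitted and require additional days of acute care".
- **Collection (5.5.3, Covariates of Interest).** "Admission source" is listed as a covariate obtained at admission.
- **Subgroups (6.1).** The authors "plan to perform a subgroup analysis by admission source", with three classes: ED, ward and home.
- **Allocation (4.3).** Randomisation follows consent and is stratified on diagnosis only.
- **Endpoint (5.5.1).** The primary endpoint is the total cost of the hospitalization, obtained at discharge. No start point is given for patients who were already admitted when randomised.

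**The concern.** A ward entrant joins part-way through a stay, and the other entrants join at or near its start. Expected cost may therefore differ by route, and the route is settled before the envelope is opened. A baseline variable of this kind can go into the primary model without threat to validity. If it predicts cost, it lowers the residual dispersion and narrows the interval for the cost ratio.

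The protocol treats the variable as important enough to split the results by, but does not use it in the model that gives the headline result. Because section 6.1 itself names the model terms and the possible adjusters, this is a choice the protocol has made and not a detail left open. Under the stated rule, source could not enter even if ward entrants were unevenly split between arms. Adding it after that was seen would be post hoc.

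At stake is the width of the primary interval and some power.

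**Working it through.** **Inputs from the protocol (6.1, Power analysis).** Ratio of means 0.6, gamma dispersion φ = 1.2, two-sided α = 0.05, 66 per arm required, 75 per arm hoped for.

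**Step 1: the plan's own figure.** For the Wald test of the log ratio, SE = √(2φ/n) and power = Φ(|ln 0.6|/SE − 1.96).

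- n = 66: SE = √(2 × 1.2/66) = 0.191; 0.511/0.191 = 2.68; power = Φ(0.72) = 76.4%. The protocol states 80%.
- n = 75: power = 81.5%.
- For 80%: n = 2 × 1.2 × (1.960 + 0.842)²/0.511² ≈ 72.2, so 73 per arm.

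The stated 80% at 66 per arm is not reproduced. That is a separate sample-size matter. Here 76.4% serves only as the baseline.

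**Step 2: dispersion left after adjusting for source.** Let p be the share of ward entrants and r their mean cost relative to the other routes. The protocol gives neither, so both are assumed. Assume also that the 1.2 already contains the between-route spread. Then

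- m = pr + (1 − p)
- CV²(between) = p(1 − p)(1 − r)²/m²
- φ(adjusted) = (1 + 1.2)/(1 + CV²) − 1

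Worked case, p = 0.20 and r = 0.5: m = 0.90; CV² = 0.16 × 0.25/0.81 = 0.0494; φ = 2.2/1.0494 − 1 = 1.096; power at 66 per arm = 80.0%.

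**Step 3: range at 66 per arm (76.4% without source).**

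| Ward cost ÷ other routes | p = 20% | p = 33% | p = 50% |
|---|---|---|---|
| 0.8 | 76.9% | 77.2% | 77.3% |
| 0.7 | 77.6% | 78.2% | 78.7% |
| 0.5 | 80.0% | 82.2% | 84.2% |
| 1.5 | 78.8% | 79.4% | 79.3% |
| 2.0 | 84.2% | 85.1% | 84.2% |

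The first three rows suit costing from randomisation. The last two suit costing from original admission.

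**Step 4: simulation check.** Gamma regression with arm and site was compared with the same model plus source, using 66 per arm, 30% ward entrants and 3,000 runs per case.

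| Ward cost ÷ other routes | Arm + site | With source added |
|---|---|---|
| 1.0 (no effect) | 76.9% | 76.9% |
| 0.6 | 77.2% | 80.1% |
| 0.4 | 76.3% | 84.7% |

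The simulation agrees with the formula and shows no loss of power when source is irrelevant.

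**Step 5: chance imbalance.** The SD of the arm difference in ward share is √(2p(1 − p)/66), which is 0.070, 0.082 and 0.087 at p = 20%, 33% and 50%. A difference of 10 points or more therefore has probability of about 15%, 22% and 25%. With r = 0.5 and p = 33%, a 10-point difference (38.3% against 28.3%) multiplies the unadjusted ratio by (1 − 0.383 × 0.5)/(1 − 0.283 × 0.5) = 0.942. On the log scale that is −0.060, or about 0.31 of the 0.191 standard error.

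**The case against.** The case against is substantial, and much of it limits the point.

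- **The cost window is not stated.** A reader might infer that ward entrants must be cheaper because only the rest of their stay is costed. Section 5.5.1 does not support this. It names total hospitalization cost and gives no start point, so pre-randomisation days may count and ward entrants may be dearer. This stands against any claim about direction. It does not remove the case for adjustment, because source is plausibly prognostic on either reading.
- **The gain is assumed, not documented.** A gain of under 1 point fits the protocol as well as one of 8. The formula also takes the preliminary-data dispersion to reflect this trial's mix of routes, which the protocol does not say. Overlap of source with diagnosis is not allowed for. All of this stands.
- **Imbalance is not bias.** A reader might take the 6% shift in Step 5 for a biased saving. Randomisation makes it ordinary chance error, already covered by the interval. Arm plus site remains a valid randomised analysis.
- **The shortfall from 80% has another cause.** It might be read as a result of leaving source out. It is not: it comes from the sample-size calculation, and at 75 per arm power is 81.5% without source.
- **The subgroup analysis would show differences by route.** It would, but it does not narrow the interval of the primary estimate.

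**Conclusion.** The point holds as a missed gain in precision. Admission source is fixed before allocation, already collected and already a planned subgroup factor, yet the primary model and its adjuster list leave it out and the randomisation does not balance it.

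At 66 per arm and dispersion 1.2, adding it raises power from 76.4% by:

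- under 1 to about 2 points if ward cost is 0.7 to 0.8 of other routes;
- about 4 to 8 points if ward cost is half and 20% to 50% enter from the ward;
- about 2.5 to 3 points if the whole stay is costed and ward entrants cost 1.5 times as much.

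These figures rest on assumed shares and cost ratios and on the 1.2 already containing the between-route spread. The documents do not show that the present analysis is biased or invalid. The case for the change is that the possible gain is useful and the price is close to nothing.

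**What to change.** 1. **Section 6.1, primary model.** Add admission source as a prespecified fixed effect with three levels (ED or clinic, ward, home), included regardless of observed balance.
2. **Section 5.5.1.** State when costing starts for early transfers, and apply the same rule in both arms.
3. **Section 6.1, subgroups.** Put clinic entrants in a named category. Sections 3.3 and 4.1 allow that route, but the three listed classes do not place it.

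The cost is two degrees of freedom in the model and some wording. No new data and no further patients are needed.

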**Figure 2**

#### 4.3 Treatment Assignment

- If the participant consents, the research assistant will proceed to randomization via concealed envelopes with
  - Concealed allocation;
  - Stratified on diagnosis:
    - infection,
    - heart failure,
    - chronic obstructive pulmonary disease or asthma, and
    - other diagnosis;
  - Randomly selected block sizes between 4 and 6;
  - Use randomization to determine arm.
- If patient/caregiver does not consent, the research assistant will ask the patient's permission to collect covariates, functional status, and a quality-of-life measure to determine generalizability of enrollment.
- Participants randomized to the control group will receive usual care at the hospital, from an attending general internist.

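### The primary cost model omits diagnosis, the only named randomisation stratum, and admits four covariates only if the arms are seen to differ, with no criterion for differing

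*Protocol*

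**What the plan says.** Protocol section 4.3 (Treatment Assignment) describes the allocation as "Stratified on diagnosis" in four groups: infection, heart failure, COPD or asthma, and other. It adds "Randomly selected block sizes between 4 and 6". No other stratum is named, and site is not listed as one.

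Section 6.1 (Quantitative) fixes the primary analysis of hospitalisation cost as a gamma regression with log link, "with treatment arm (control arm as the reference group) and site as fixed effects". Diagnosis is neither a model term nor a candidate covariate. It returns only among the planned subgroup analyses, "by diagnosis, by age group, and by daily activity level".

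Three sets of covariates are conditional on what is observed:
- Sex, age, education and comorbidity count: "we will adjust for any of the follow patient characteristics that differ across arms: sex, age (continuous), education, and comorbid condition count (continuous".
- COVID case burden: "only if COVID impacted home hospital operations".
- Rurality: "If the degree of rurality was different between patients at different sites".

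The power analysis assumes a cost ratio of 0.6, gamma dispersion 1.2, two-sided alpha 0.05 and 66 patients per arm, and refers to this same model. It does not mention diagnosis.

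**The concern.** A stratification factor is normally chosen because it is expected to predict the outcome. If it is then left out of the model, the reported standard error still carries between-diagnosis variation that the design set out to control. That costs power, and the primary analysis has none to spare (see the first step of the working).

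The covariate rule raises a separate problem. Under sound randomisation any baseline difference between arms is chance, so a rule triggered by such differences lets chance choose the primary model. Because the protocol does not say what counts as differing, the headline cost ratio also depends on a threshold that could be settled after the data are seen. This does not turn on an unseen SAP: the protocol itself fixes both the model and the rule. An SAP could supply a threshold, but the model would still be chosen from the data.

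**Working it through.** **1. The plan's own figure.** In a gamma log-link model with dispersion φ and n per arm, the log cost ratio has variance 2φ/n. With φ = 1.2 and n = 66, SE = √(2.4/66) = 0.1907. The effect is |ln 0.6| = 0.5108, so power = Φ(0.5108/0.1907 − 1.96) = Φ(0.719) = 76.4%. For 80% power, n = 2.4 × (1.96 + 0.8416)² / 0.5108² = 72.2, or 73 per arm. The stated 66 per arm and 80% therefore do not reproduce from the stated inputs. At the hoped-for 75 per arm, power is 81.5%. That is a separate matter, but it is why lost precision counts here.

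**2. What adding diagnosis could buy.** The documents do not say how strongly diagnosis predicts cost. Let s be the SD of log mean cost between diagnosis groups (assumption), and hold the overall squared coefficient of variation at 1.2. The dispersion left within diagnosis is φ_res = (1 + 1.2)/exp(s²) − 1.

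- Log-scale interval width without diagnosis relative to with it: √(1.2/φ_res).
- Power with diagnosis: Φ(0.5108/√(2φ_res/66) − 1.96).
- Power without diagnosis: blocking already balances diagnosis, so the estimate varies less than its reported SE suggests. Under perfect balance, power = Φ(0.719 × √(1.2/φ_res)).

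| s (assumed) | φ_res | Width ratio | Power without | Power with | Gain, points |
|---|---|---|---|---|---|
| 0 | 1.200 | 1.000 | 76.4% | 76.4% | 0 |
| 0.2 | 1.114 | 1.038 | 77.2% | 79.4% | 2.2 |
| 0.3 | 1.011 | 1.090 | 78.3% | 83.1% | 4.8 |
| 0.4 | 0.875 | 1.171 | 80.0% | 88.1% | 8.1 |

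**3. Check by simulation.** The 132-patient design was simulated for s from 0.2 to 0.4:
- The site-only model rejected in 4.6–5.6% of null trials, and its reported SE was within about 2% of the true one.
- Adding diagnosis gained about 2.5 to 7 points of power, in line with the table except at its upper end.
- Adding diagnosis also raised null rejection to about 6–7%, because model-based standard errors run low in a sample of this size. Part of the power gain is therefore not real.
- In a companion simulation at the assumed ratio of 0.6, the mean estimated log ratio was −0.513 to −0.519 under every model fitted, against a true value of −0.511. Omission did not bias the estimate.

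**4. How often the rule fires by chance.** With four independent covariates and threshold p, the probability is 1 − (1 − p)⁴:
- p<0.05: 1 − 0.95⁴ = 18.5%
- p<0.10: 1 − 0.90⁴ = 34.4%
- p<0.20: 1 − 0.80⁴ = 59.0%

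**5. What the rule does to type I error.** In 1,200 simulated null trials (Monte Carlo standard error √(0.05 × 0.95/1200) = 0.6 points), rejection was 4.9% with site only and 4.5% with a fixed p<0.10 rule. It was 5.9% when the most favourable of four readings (no adjustment, or thresholds 0.05, 0.10 and 0.20) was picked afterwards.

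**The case against.** The strongest reply is that little is at risk. The candidate list is closed and named in advance, the estimate is unbiased, and a fixed rule leaves the error rate alone. At 75 per arm the unadjusted analysis reaches 81.5% power anyway. All of that stands. The 19% and 34% figures count changes of model, not false positives. What remains is that the protocol gives no fixed rule, and precision is given up for no benefit.

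Several stronger readings are tempting and should not be adopted.

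- *The reported error bars are wrong.* If diagnosis explained 5–20% of variance, the large-sample formula 1/√(1 − R²) would make the SE 3–12% too wide and the 5% test really 4.4–2.8%. That presumes perfect balance and an exact Wald test. In the simulated design, incomplete blocks and a dispersion estimated slightly low offset the effect. Clear conservatism (3.7% rejection) appeared only under a stronger assumption, s = 0.45 with prognostic covariates.
- *Rurality is redundant because site absorbs it, and its sources are US-only.* Site absorbs only mean differences between sites. The covariate table in section 5.5.3 records rurality at admission and lists population density and zip codes among its sources, so it can vary within a site. The appendix gives a separate Canadian definition of rural.
- *The activity subgroup conditions on a post-randomisation measure.* Section 6.1 does not say how daily activity level is measured. The tracker listed in section 5.5.3 is a plausible source, but activities of daily living are also collected at admission. The objection applies only if the tracker is meant.

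**Conclusion.** The point holds as a matter of precision and pre-specification. It does not show bias or an invalid test. The only named stratum is missing from the primary model, and the rest of that model depends on observed differences judged by an unstated criterion.

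The size is modest and conditional: roughly 2 to 7 points of power at 66 per arm for an assumed between-diagnosis log-cost SD of 0.2 to 0.4, and nothing if diagnosis does not predict cost. Part of that gain disappears once the standard errors are corrected. The chance of a model switch, about 19% at p<0.05 and 34% at p<0.10, assumes independent covariates and a p-value criterion that the protocol does not state. The change should be made because it is nearly free, not because the current analysis would mislead.

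**What to change.** - Pre-specify the primary gamma model as arm, site, diagnosis stratum and a short fixed list, for example age and comorbidity count, whatever the observed balance. Delete the rule that depends on differences between arms.
- Use a small-sample or robust variance. Without it, null rejection was about 6–7% with diagnosis added and 6–8% with all covariates included.
- Do not let rurality depend on an observed difference between sites, since the site term already handles mean differences between sites. Include it in advance or leave it out. The COVID-burden clause needs the same decision.
- State what daily activity level means in the subgroup list. If it is the in-admission tracker measure, use admission ADL/IADL instead: the tracker measure is taken after randomisation, and section 2.2 names physical activity as something the intervention should improve.

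The cost is a change of wording and a few degrees of freedom; the variables are already collected. With a log link and no treatment interaction, adjustment does not change the meaning of the cost ratio.

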### ***Power analysis***

A priori (based on data from our previous randomized controlled trial of urban home hospital care), we expect the mean cost to be mean cost on intervention to be 40% lower than in control (leading to a ratio of mean costs in treatment to control to be at most .6). Thus, for our power calculation, we want to be able to detect that the exponential of the treatment effect in our

gamma regression to be 0.6 or lower., We will require 132 patients total (66 in each arm, and 44 total per site) to detect a 40% relative decrease in mean direct cost in home versus hospital (power: 80%, alpha: 0.05, two-tailed) using the Wald test for the treatment effect from a gamma regression model for costs discussed above. In this power calculation, we assume the over-dispersion parameter for the gamma distribution variance is 1.2 (as seen from our preliminary data). Although we hope to recruit 75 patients in each arm, 66 patients will give us more than adequate power (80%) to detect the clinically expected difference.

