Secondary outcomes require slightly larger samples sizes at 80% power (with Type 1 error of 1%, approximately the type 1 error when using the Benjamini-Hochberg method as noted above). For Cost, discharge to 30-days, using a gamma regression model similar to total costs, with 66 patients in each arm, we have 80% to see an expected 65% reduction in the mean for intervention to control (we assume the over-dispersion parameter for the gamma distribution variance is 2.8 as seen from our preliminary data). For number of hours per day laying down (equivalently, % of day Lying down), using a negative binomial regression model with a logistic link with treatment and site effects, with 66 patients in each arm, we have over 90% to see an expected 65% reduction in the number of hours lying down for intervention to control (we assume the over-dispersion parameter for the negative binomial distribution is 1.4 as seen from our preliminary data). For percent with 30-day readmission, using logistic regression model with treatment and site effects, with 66 patients in each arm, we have 80% to detect on odds ratio of 0.25 for intervention on control (assuming the percent 30 day readmission in controls is 23% as seen in preliminary data). For the number of days at home, using a log-normal distribution with treatment and site effects, with 66 patients in each arm, we have over 80% to see an expected 65% increase in the number days at home for control to intervention (from 29 days to 48, days assuming the over-dispersion parameter for the negative binomial distribution is 1.4).

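### With about 20 expected readmissions, maximum-likelihood logistic regression would modestly overstate a large true effect; naming Firth estimation is a cheap improvement

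*Protocol*

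**What the plan says.** Protocol Section 6.1 carries the primary outcome's model over to the secondary outcomes: "We will use this same multivariable regression approach for secondary outcomes, using logistic regression for binary outcomes (e.g., readmissions". In that model, treatment arm and site are fixed effects. Sex, age, education and comorbidity count are added where they differ between arms, COVID burden if it affected home hospital operations, and degree of rurality if it differed between sites. The section names no small-sample method and sets no limit on the number of covariates.

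The Power analysis part of the same section describes readmission more narrowly, "using logistic regression model with treatment and site effects, with 66 patients in each arm". Its claim for this endpoint reads: "we have 80% to detect on odds ratio of 0.25 for intervention on control". The event rate behind that claim is given as an assumption: "assuming the percent 30 day readmission in controls is 23% as seen in preliminary data". The total is "132 patients total (66 in each arm, and 44 total per site" and the recruitment goal is larger ("we hope to recruit 75 patients in each arm"). Secondary outcomes are powered "with Type 1 error of 1%, approximately the type 1 error when using the Benjamini-Hochberg method as noted above".

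**The concern.** Logistic regression named without qualification normally means maximum likelihood. With few events per fitted coefficient, maximum-likelihood log odds ratios are biased away from zero, and some data sets separate, so that no finite estimate exists. The plan's own inputs put readmission in that region, and the optional covariates make it worse.

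Readmission is a listed secondary endpoint and is named in Secondary Aim 1. If home hospital care does lower readmission strongly, the reported odds ratio would on average look somewhat better than the truth. The concern is the estimator, not the stated power.

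**Working it through.** **Inputs (Section 6.1, Power analysis).** 66 per arm; control risk 0.23; odds ratio 0.25; type I error 1% for secondary outcomes. Two-sided testing is assumed, because only the primary outcome states it ("power: 80%, alpha: 0.05, two-tailed").

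**Expected events.**
- Control odds = 0.23/0.77 = 0.2987; home odds = 0.25 × 0.2987 = 0.0747; home risk = 0.0747/1.0747 = 0.0695.
- Events = 66 × 0.23 + 66 × 0.0695 = 15.2 + 4.6 = 19.8 (5th to 95th percentile 13 to 26).
- At 75 per arm: 75 × (0.23 + 0.0695) = 22.5.

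**The plan's own power figure.** For the log odds ratio, SE² = 1/(66 × 0.23 × 0.77) + 1/(66 × 0.0695 × 0.9305) = 0.0856 + 0.2343 = 0.320, so SE = 0.566. Then |ln 0.25|/SE = 1.386/0.566 = 2.45, and power at two-sided 1% = Φ(2.45 − 2.576) ≈ 45%. Other standard tests give 50 to 54%. The stated 80% does not reproduce. That is a separate matter, which a change of estimator does not repair.

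**Events per slope.**
- Arm 1 + site 2 = 3 slopes: 19.8/3 = 6.6.
- Adding sex, age, comorbidity count and education as three levels (an assumption; the coding is not stated): 8 slopes, 19.8/8 = 2.5.
- Arm, site, four patient terms (education as one term), COVID burden and rurality: 9 slopes, 19.8/9 = 2.2.

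**Bias at a true odds ratio of 0.25** (several independent simulations, 1,500 to 6,000 trials per scenario; covariates unrelated to outcome; non-converged maximum-likelihood fits left out of the means). The odds ratios are exponentials of the mean log odds ratio.

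| Model | ML odds ratio | Excess in log OR | Excess / sampling SD | Firth odds ratio |
|---|---|---|---|---|
| 66 per arm, 3 slopes | 0.22–0.23 | 0.08–0.12 (6–8%) | 0.117/0.633 = 0.18 | 0.24–0.25 |
| 66 per arm, 8 slopes | 0.21 | 0.19 | 0.19/0.65 ≈ 0.3 | 0.25 |
| 66 per arm, 9 slopes | 0.20–0.21 | 0.19–0.20 (14–15%) | 0.189/0.689 = 0.27 | 0.25 |
| 75 per arm, 9 slopes | 0.21 | 0.17 (12%) | 0.172/0.653 = 0.26 | 0.25 |

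The ratios in the fourth column come from single runs. In row two the SD is √(0.68² − 0.19²) = 0.65, from a root-mean-square error of 0.68.

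**Total error.** The root-mean-square error of the log odds ratio falls under Firth from 0.65 to 0.57–0.60 (3 slopes) and from 0.68–0.70 to 0.54–0.58 (8 slopes). Bias and variance therefore improve together.

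**Separation.** About 1% of maximum-likelihood fits at 66 per arm separate or fail to converge (0.6 to 1.2% across runs). Firth still returns a finite estimate.

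**Smaller or no effect.** At a true odds ratio of 0.5, maximum likelihood gives 0.47–0.48 with 3 slopes and 0.45 with 9. At an odds ratio of 1 there is no bias, and the 9-slope model rejects in 5.2–5.4% of trials at 5% and 1.1% at 1%. Interval coverage was 94–98% throughout.

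**The case against.** **The protocol does not say maximum likelihood.** Estimator, test and interval method are often left to a statistical analysis plan, which is not shown. This stands in part: naming logistic regression is not an error, and Firth is one way of fitting it. But Section 6.1 already fixes the model and the covariate rule, and unqualified wording will be run as maximum likelihood by default.

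**Most of the covariates are conditional.** True. Only the three-slope model is certain, and there the excess is 6–8% on the log scale. Holding readmission to arm and site, as the Power analysis describes it, would reduce the bias but not remove it.

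**The bias depends on the scale.** It appears in the mean log odds ratio and in the median odds ratio (about 0.21 to 0.23). On the arithmetic mean of the odds ratio itself, maximum likelihood gives 0.27 (arm and site) and 0.25 (with covariates), and Firth 0.29. This stands. The log scale is the one on which estimates and intervals are built, but the gain should be described on that scale only.

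**It depends on the covariates assumed.** With prognostic covariates (log odds ratio 0.3 per SD) and the full set fitted, the excess was 16%. When only two terms were fitted, maximum likelihood averaged 0.248 and Firth exp(−1.298) = 0.273. Leaving out prognostic variables pulls both towards 1 and masks the bias.

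**A reader might infer that a planned Wald test wastes power.** The protocol does not support this: it names the Wald test only for the cost model and no test for readmission. Nor is the gain specific to Firth. At the 1% level, Wald rejects in 42–46% of simulated trials, the Firth likelihood-ratio test in 48–54% and an ordinary likelihood-ratio test in 55–57%. The last has slight inflation under the null (1.2–1.4%).

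**Conclusion.** The point holds as a modest one. At the plan's own inputs there are about 20 readmissions for 3 to 9 or more slopes. If the assumed odds ratio of 0.25 is true, maximum likelihood overstates it on the log-odds scale by 6–8% in the model that is certain to be fitted, and by up to about 15% if all optional terms enter. That is 0.2 to 0.3 of a standard error.

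A reader might infer that the published result will necessarily flatter home hospital care, or that a false positive could arise. Neither follows: the bias enlarges a real effect, shrinks as the effect shrinks, vanishes under the null, and leaves type I error and coverage near nominal.

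The figures rest on the protocol's event rate and odds ratio, on the reading of logistic regression as maximum likelihood, and on assumed covariate distributions and education coding.

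**What to change.** In Section 6.1, state that 30-day readmission will be analysed by Firth penalised-likelihood logistic regression, with profile penalised-likelihood confidence intervals and tests. Keep treatment arm and site as planned.

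The cost is one sentence and standard software. The reported odds ratio will usually be slightly closer to 1, and so less favourable to home hospital care if the effect is real. In return, the log-scale bias is largely removed, total error falls, type I error is held (4.9–5.6% at the 5% level in simulation), and an estimate exists even when the data separate.
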